467 we will ask all participants about prescription drug use regardless of their use of other substances.  
468 Following the format of the S2BI, questions about other psychoactive substances including illegal  
469 drugs (such as cocaine or Ecstasy), inhalants (such as nitrous oxide), and herbs and synthetic drugs  
470 (such as salvia, "K2" or bath salts) will be asked only if participants answer yes to either alcohol,  
471 marijuana, or tobacco use.

472 **Criterion standard for substance use disorder diagnosis:** If participants answer no to past 12  
473 month alcohol, marijuana, or tobacco use they will be asked a question about lifetime use of these  
474 substances. Questions about lifetime use were taken from the Computerized Diagnostic Interview  
475 Schedule for Children – 4 (DISC-IV).

476 **Alcohol safety screen:** We will include questions about frequency and severity of alcohol use that  
477 will be used as safety flags. If a patient reports consuming 10 or more drinks containing alcohol in the  
478 past three months, or using sedatives in combination with alcohol, the RA will notify the primary  
479 clinician (See Adverse Event Criteria and Reporting Procedures)

480 **Prescription medication misuse:** Abuse of prescription medications among youth has risen  
481 dramatically in recent years. We will ask questions to assess if participants take medication as  
482 prescribed by their doctor. We will also assess medication diversion, with a specific interest in patients  
483 who are being prescribed stimulant medications. These questions were adapted from previous  
484 studies on prescription medication misuse among adolescents.

485 **Criterion standard substance use frequency measure:** Each participant who reports any alcohol  
486 use will complete a 90-day Timeline Follow Back (TLFB) calendar that records frequency and quantity  
487 of alcohol use and frequency of marijuana use. The 90-day TLFB has been demonstrated to be both  
488 valid and reliable in adolescents. Participants will complete the TLFB on the computerized tablet  
489 following completion of the assessment battery. The TLFB is self-administered; participants will view  
490 an electronic calendar of the past 90 days and will input if they used marijuana on a given day and/or  
491 number of drinks consumed on a given day. If participants have not used marijuana or consumed a  

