## 2.0 SUMMARY OF STUDY DESIGN AND PROCEDURES

### 2.1 Study Objectives

#### 2.1.1 Primary Objectives (Reference: Protocol: p.1, p.8, p.9)

The primary goal of this project is to develop a tailored screening, brief intervention and referral to treatment (SBIRT) model for youth with chronic medical conditions (YCMC) for delivery at point of care during a routine healthcare visit, through conducting a rigorous randomized control trial among adolescent patients with type-1 diabetes (T1D) or rheumatologic conditions.

Building onto an earlier phase of this project (Validating Adolescent SBIRT Measures), we will assess the validity and acceptability of a subset of brief substance-specific questions that are strongly associated with reports of current substance use behaviors and harms and that predict future substance use behaviors and harms.

Screening, tailored feedback and psychoeducation will all be delivered electronically. The brief intervention will target perceived risk of harm of a given substance, knowledge about substances, knowledge of disease specific and medication interactions, and intentions to use. These intermediary measures may serve as proxy markers that can be tracked and may predict substance use trajectories during a long term follow up period.

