### **2.2.5 Measures (Reference: Protocol p. 9-18)**

**Health information:** Past medical history may inform a participant's decisions to use or abstain from alcohol and other drug use. Youth may use illicit substances to self-medicate, or may avoid substances because of specific health concerns. We will ask participants to report past medical history, and to rate their overall health. We will use previously validated questions to assess these domains. A question on past medical history about being treated with prescribed medications for anxiety, depression, or ADHD was created novel for this battery.

**Other factors that may affect substance use:** Multiple components of the day to day life of youth may predict a relationship to substance use patterns. Predictors of interest for this project include social support, parental monitoring and communication, sleep, and family medical history.

**Current mental health status:** The PHQ-2 is a self-administered, 2-item scale for detecting depression using DSM-IV diagnostic criteria. The PHQ-2 has been studied extensively in large populations and

comes with considerable evidence for its validity. The PHQ-2 has been used extensively in primary care settings and adolescent populations. We will be administering the full PHQ-2 at baseline, 6 month follow up, and 12 month follow up.

The GAD-2 is a self-administered, 2 item scale to screen for anxiety disorders. It has high sensitivity and specificity for detecting generalized anxiety disorder and has been used in primary care settings. We will be administering the full GAD-2 at baseline, 6 month follow up, and 12 month follow up.

**Alcohol, tobacco, marijuana, and use of other substances:** We will administer a series of questions about frequency of substance use and validate them against the criterion standard TLFB.

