**Substance use screen:** We will administer the Screening to Brief Intervention (S2BI) to ask about alcohol, tobacco, marijuana, prescription drug, and other substance use over the past 12 months. S2BI was developed at BCH with support from NIDA. In the original S2BI, questions on prescription drug use are asked only if patients answer yes to using alcohol, marijuana, or tobacco. In this study we will ask all participants about prescription drug use regardless of their use of other substances. Following the format of the S2BI, questions about other psychoactive substances including illegal drugs (such as cocaine or Ecstasy), inhalants (such as nitrous oxide), and herbs and synthetic drugs (such as salvia, “K2” or bath salts) will be asked only if participants answer yes to either alcohol, marijuana, or tobacco use.

**Criterion standard for substance use disorder diagnosis:** If participants answer no to past 12 month alcohol, marijuana, or tobacco use they will be asked a question about lifetime use of these substances. Questions about lifetime use were taken from the Computerized Diagnostic Interview Schedule for Children – 4 (DISC-IV).

**Alcohol safety screen:** We will include questions about frequency and severity of alcohol use that will be used as safety flags. If a patient reports consuming 10 or more drinks containing alcohol in the past three months, or using sedatives in combination with alcohol, the RA will notify the primary clinician (See Adverse Event Criteria and Reporting Procedures)

**Prescription medication misuse:** Abuse of prescription medications among youth has risen dramatically in recent years. We will ask questions to assess if participants take medication as prescribed by their doctor. We will also assess medication diversion, with a specific interest in patients who are being prescribed stimulant medications. These questions were adapted from previous studies on prescription medication misuse among adolescents.

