**Criterion standard substance use frequency measure:** Each participant who reports any alcohol use will complete a 90-day Timeline Follow Back (TLFB) calendar that records frequency and quantity of alcohol use and frequency of marijuana use. The 90-day TLFB has been demonstrated to be both valid and reliable in adolescents. Participants will complete the TLFB on the computerized tablet following completion of the assessment battery. The TLFB is self-administered; participants will view an electronic calendar of the past 90 days and will input if they used marijuana on a given day and/or number of drinks consumed on a given day. If participants have not used marijuana or consumed a drink in the past 90 days, they will click through the calendar leaving the days blank. On the last screen they will be prompted to confirm that they did not select any days. The tool will be programmed to calculate total days of use and number of drinks.

**Intermediary measures:** We hypothesize that the following questions may serve as intermediary measures to predict long term substance use outcomes.

**Time spent with alternative activities:** Studies have shown that involvement in school based extra-curricular activities is generally related to less substance use among adolescents except in the case of athletic participation which has shown a positive relationship to substance use. We are interested in the number of hours participants spend per week engaged in different activities.

**Academic and extracurricular performance:** Engagement, performance, and interest in academics and extracurricular activities, as well as disciplinary consequences may be indicators of current or future substance use. We will ask participants about personal consequences related to substance use. We are interested in consequences related to school such as academic performance, their commitment to school and extra-curricular activities, and how often they receive detention.

**Perception of overscheduling:** We will ask questions based on whether or not adolescents view themselves as overscheduled taken from the Measure of Perceived Over-Scheduling (MOPS) scale. We selected three items from the MOPS scale one from each factor measurement: pressure from external forces to participate in activities, feeling overwhelmed by participation, and preference for one's activities.

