#### **Defining Outcomes**

Primary Outcome(s): Past 3-month alcohol use measured by a Brief Frequency variable for alcohol use.

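### The brief use questions are validated against the TLFB calendar only among youth who already report alcohol use, so sensitivity is overstated by the unknown share of drinkers who deny

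*Supplement*

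**What the plan says.** SAP 2.1.1 (Primary Objectives) includes the aim that "we will assess the validity and acceptability of a subset of brief substance-specific questions". SAP 2.2.5 (Measures) names the reference: "We will administer a series of questions about frequency of substance use and validate them against the criterion standard TLFB".

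The same section then restricts who receives that reference: "Each participant who reports any alcohol use will complete a 90-day Timeline Follow Back (TLFB) calendar". Protocol section D carries the same rule, in the sentence that opens "Each participant who reports any alcohol". Neither document says which question decides, or over what period.

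Three further points bear on how wide the entry rule is:

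- The substance use screen asks about "alcohol, tobacco, marijuana, prescription drug, and other substance use over the past 12 months".
- Of those who answer no, the SAP says "they will be asked a question about lifetime use of these substances".
- For calendar takers with no use in the last 90 days, the SAP says "they will click through the calendar leaving the days blank". The last screen then asks them to confirm that no day was selected.

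Protocol section A (Specific Aims) lists the TLFB as a component of each assessment battery and mentions no entry rule.

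SAP 11.0, in the update dated 6/27/2019, defines the primary outcome as "Past 3-month alcohol use measured by a Brief Frequency variable for alcohol use".

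**The concern.** Whether a participant gets the reference measurement depends on a self-report of the same kind as the one being validated. A youth who denies alcohol use and would have entered drinks on the calendar is never observed as a false negative. This is partial verification: accuracy is estimated only in those whose earlier answer opened the reference test.

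At stake is the validity objective. Sensitivity would be reported for youth who admit use but could be read as applying to all participants. Under-reporting is the main weakness of self-reported adolescent drinking, and this rule hides its most complete form. The documents give some reason to expect it. Flagged alcohol answers go to the clinician, who decides whether parents are told (Protocol E, SAP 7.0). In an earlier survey, 15% of patients or parents were reluctant to share youth alcohol data with a provider outside the hospital (Protocol C).

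**Working it through.** The plan states no sensitivity, specificity, agreement target or sample size for the validation, so there is no figure of its own to reproduce.

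**Inputs from the documents**
- Enrolment: 450 (SAP 9.0).
- Reported past-year alcohol use in the preliminary study: 30.8% of the whole sample, 36.5% of high school youth (Protocol C).

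**Assumptions (not in the documents)**
- m, the share of true 90-day drinkers who deny alcohol use at the entry question: 5%, 10% or 20%.
- Those who deny at entry also deny on the brief question.
- Two thirds of those who reach the calendar drank in the past 90 days.
- Specificity of the brief question among calendar completers: 0.95.

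**Step 1. Coverage under a past-year entry rule**
- 450 × 0.308 = 138.6, so about 139 get the calendar and 311 do not.
- 450 × 0.365 = 164.3, so about 164 get the calendar and 286 do not.
- A lifetime entry rule would cover more.

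**Step 2. Bias in sensitivity**

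Observed sensitivity is taken among drinkers who reached the calendar. These are a share (1 − m) of all drinkers, and the remaining m are all missed. Hence true sensitivity = observed sensitivity × (1 − m), and the overstatement is 1/(1 − m).

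| m | 1/(1 − m) | True value if observed is 1.00 | True value if observed is 0.80 |
|---|---|---|---|
| 5% | 1.05 | 0.95 | 0.76 |
| 10% | 1.11 | 0.90 | 0.72 |
| 20% | 1.25 | 0.80 | 0.64 |

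**Step 3. Hidden against visible false negatives, at 36.5%**

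Drinkers on the calendar: 450 × 0.365 × 2/3 = 109.5.
- Hidden = 109.5 × m/(1 − m): 5.8, 12.2 and 27.4 for m = 5%, 10% and 20%. At 30.8% the counts are 4.9, 10.3 and 23.1.
- Visible = 109.5 × (1 − sensitivity among completers): 5.5 at 0.95, 21.9 at 0.80, 54.8 at 0.50.

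A poor question therefore still shows many misses; those of full deniers are not among them.

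**Step 4. Direction for specificity**

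With m = 10% at 36.5%, non-drinkers number 450 − 109.5 − 12.2 = 328.3, of whom 54.75 reached the calendar. Overall specificity = (0.95 × 54.75 + 273.55)/328.3 = 0.99, against 0.95 observed. This bias runs against the question.

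**Step 5. A question with no information**

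In a simulation with 36.5% on the calendar, brief answers were drawn at random from the distribution of calendar values. Among completers the result is Spearman 0.00, sensitivity 0.67 and specificity 0.33. If deniers were scored as calendar zeros, the same question would show Spearman 0.55 and specificity 0.89, with sensitivity still 0.67.

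**The case against.** The strongest reply has four parts.

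**The entry rule seems wider than the 3-month question.** The screen covers 12 months, a lifetime question follows a no, and the blank click-through implies calendar takers without recent use. A youth who reports earlier drinking but answers zero for the past three months would then get a calendar, and that false negative can be seen. This stands. A reader might infer that no false negative is ever visible; that would follow only if the validated question itself opened the calendar, and no section says so.

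**A poor question would not pass unnoticed.** Step 5 shows that one carrying no information is exposed among completers, and Step 4 shows specificity pulled down. This also stands. A reader might infer that nearly any question would look valid. The documents do not support that: it comes close to true only if the question opens its own calendar or skipped calendars are entered as zeros, and neither is planned.

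**The harm to the trial is indirect.** SAP Table A and section 6 contain no analysis of brief questions against the TLFB, and the Study Design text places the accuracy assessment in the larger cohort study. The Protocol D measures table says the brief frequency measures were developed for an earlier project. A reader might infer that the 2019 primary outcome rests on this validation, but SAP 11.0 does not cite it. What remains is that SAP 2.1.1 still lists validity among the primary objectives, and nothing elsewhere repairs the restriction.

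**The calendar is self-report too.** Youth who deny once may deny again, and an arm-related shift in reporting could move both measures. This limits what the remedy can recover. It does not justify treating unmeasured agreement as known.

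**Conclusion.** The point holds as a limit on the validity objective. Validation is conditional on reporting alcohol use under an undefined rule, so whole-sample sensitivity cannot be estimated and the observed figure is too high by 1/(1 − m). The factor is 1.05 to 1.25 for an assumed m of 5% to 20%; the documents give no value for m, and data collected under the rule cannot supply one. Under a past-year rule, about 286 to 311 of 450 participants would have no reference value; this rests on the preliminary study's rates applying here.

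The conclusion does not extend to the randomised comparison of the 2019 primary outcome, which does not use the calendar. This is a worthwhile and cheap improvement to the measurement part of the plan.

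**What to change.** **If assessments are still being collected.** In SAP 2.2.5 and Protocol D, give the 90-day TLFB to every participant at each assessment, as Protocol section A already lists it. Non-users would use the existing blank click-through and confirmation. State the validation analysis in SAP section 6:

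- sensitivity and specificity of reported past-3-month use against any use on the calendar, in all participants;
- agreement on number of days among drinkers only;
- each with a 95% confidence interval, and shown by arm at follow-up.

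**For data already collected under the skip rule.**

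- Name the question and recall window that opened the calendar.
- Do not score skipped calendars as zero.
- Restrict agreement to those who completed the calendar.
- State that whole-sample sensitivity is not estimable, and narrow any validity statement to youth who report alcohol use.

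**Cost.** Removing the skip rule adds perhaps a minute or two for non-users (an estimate, not a figure from the documents). Youth who would deny on the calendar as well are still missed. If collection has ended, only SAP wording and the scope of the validity statement change.

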We will recruit a convenience sample of adolescent patients (n=450) ages 14-17 years presenting for routine specialty care at Boston Children’s Hospital (BCH) Rheumatology and Endocrinology clinics. Eligible and consented participants will be randomized into intervention or control arms of the trial. Participants will complete a baseline assessment at the time of enrollment and then follow-up assessments at 6 and 12 months after the baseline assessment. Each assessment battery will include 1) questions about frequency of use, 2) candidates of intermediary measures that may predict future use (for example, reports about perceived harm of use), 3) substance specific measures of harms associated of use, 4) disease specific measures such as pain interference and emergency care received to assess disease burden and disease management and 5) Time Line Follow Back Calendar as criterion standard measures of substance use frequency. Those in the intervention arm will receive a computerized brief intervention composed of tailored feedback and psycho-education specific to their chronic condition. Participants in the control arm will receive brief advice on the unrelated topic of internet safety. We hypothesize that YCMC who receive the intervention will be less likely than their peers to initiate or escalate alcohol consumption 6- and 12-months post intervention. And, YCMC who receive the intervention will be less likely than their peers to initiate or escalate marijuana use 6- and 12-months post intervention.

We will recruit in tandem at baseline only, parents of those youth who are enrolled in the study, to briefly assess their attitudes, knowledge and beliefs around substance use and YCMC, as well as their opinions on various risk behaviors and health concerns. We will explore whether parent beliefs at baseline have any correlation with their child’s substance use behavior and/or attitudes and perceptions of risk.

[figure not shown]

109 **B. Background and Significance**

110 *The outstanding unmet need this project seeks to address is the need to develop accurate, feasible*  
111 *measures that inform SBIRT use among medically vulnerable youth. YCMC are uniquely vulnerable to*  
112 *short term medical consequences from substance use. Large population-based studies of adolescent*  
113 *substance use do not capture information about medical conditions and disease registries do not*  

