### **6.2 Analysis of the Primary Outcome Measure (Reference: Protocol p. 20)**

All analyses will be conducted under the principle of intention to treat; all participants will be analyzed as members of the groups to which they were originally randomized to. We will examine the impact of the psychoeducation program on alcohol use, measured from baseline to twelve months, taking into account correlations within individuals, using multivariate mixed-effects models.

Our primary outcome variables will be initiation and escalation of substance use. Initiation of use will be defined as any new use of substances at follow-up among those reporting no past-12-month use at baseline. For alcohol use, escalation will be defined as, among drinkers, any increase in number of drinks (measured by TLFB) from baseline to follow-up. For marijuana use, escalation will be defined as, among users, any increase in days of smoking marijuana (measured by TLFB) from baseline to follow-up.

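### The TLFB calendar is given only to youth who report alcohol use, yet it is the sole stated measure of marijuana escalation, so marijuana users who report no alcohol have no escalation value

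*Supplement*

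**What the plan says.** **Who gets the calendar.** SAP 2.2.5 (criterion standard frequency measure) states: "Each participant who reports any alcohol use will complete a 90-day Timeline Follow Back (TLFB) calendar". Protocol section D has the same paragraph, beginning "Each participant who reports any alcohol". Neither gives a recall window for the alcohol report.

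**What it records.** It is a "calendar that records frequency and quantity of alcohol use and frequency of marijuana use". No other source of marijuana days is named for the outcome.

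**Recent non-users.** SAP 2.2.5 adds: "If participants have not used marijuana or consumed a drink in the past 90 days, they will click through the calendar leaving the days blank". So someone let through the gate who has not used in 90 days still returns a confirmed blank calendar.

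**The outcome.** SAP 6.2 reads: "For marijuana use, escalation will be defined as, among users, any increase in days of smoking marijuana (measured by TLFB) from baseline to follow-up". Protocol section H and SAP 2.1.1 carry the same definition.

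**A conflicting statement.** Protocol section A lists the "Time Line Follow Back Calendar as criterion standard measures of substance use frequency" among the contents of each assessment battery and mentions no alcohol condition.

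**Later updates.** SAP 11.0 (6/27/2019) names past 3-month alcohol use, from a Brief Frequency variable, as the primary outcome. It does not mention marijuana escalation, and no update changes the gate.

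**The concern.** The gate concerns one substance and the outcome another. Marijuana escalation needs two calendars, baseline and follow-up. A marijuana user who reports no alcohol at baseline has no starting value, so no change can be computed even if a later calendar exists. The SAP gives no substitute measure, zero rule or missing-data rule for this person, who still meets the definition of a user.

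Less use of marijuana is one of the two stated hypotheses, beside alcohol. Users of marijuana alone may differ from dual users, so a result limited to alcohol reporters answers a narrower question than the one posed. The plan to validate the frequency items against the TLFB is also affected, because the marijuana items cannot be checked in this group.

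There is a further, conditional risk. Drinking can change after randomisation and is what the intervention targets. If the gate is applied again at follow-up, a dual user who stops alcohol might get no calendar, and the missing marijuana value would then depend on the treatment.

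**Working it through.** **1. The plan's own figure.** Protocol section I and SAP 9.0 claim power .80 with 300 completers for an odds ratio of 2.0 or more, with intervention-arm rates p of .20 to .55. Sidedness and allocation ratio are not stated; 1:1 (150 per arm) is assumed.

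- Control rate: pc = 2o/(1 + 2o), with o = p/(1 − p). At p = .20, o = .25 and pc = .50/1.50 = .333.
- Power = Φ{[|pc − p| − z·√(2p̄(1 − p̄)/n)] / √([p(1 − p) + pc(1 − pc)]/n)}, with n per arm and p̄ the mean of p and pc.
- Two-sided results: .745 (p = .20), .795 (.25), .825 (.30), .848 (.40), .837 (.50), .820 (.55). One-sided results: .836 to .911.

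The figure is met within half a point from .25 upward on a two-sided test, and throughout on a one-sided test. Sidedness is unstated, so I neither confirm nor dispute it. It uses all 300 completers, whereas marijuana escalation is defined only among users.

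**2. How many marijuana users.** Protocol section C reports past-year marijuana use of 17.2% overall and 20.6% among high school youth in an earlier cohort.

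- 300 × .172 = 51.6
- 300 × .206 = 61.8

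**3. How many lack a calendar.** The overlap with alcohol is not reported. Past-year alcohol use was 30.8% and 30.8 + 17.2 = 48.0, below 100, so the margins allow a marijuana-only share anywhere from none to all. A share must be assumed:

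- 10%: 51.6 × .10 = 5.2
- 25%: 61.8 × .25 = 15.5

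That is about 5 to 15 youth. The wider range below shows sensitivity; power is two-sided for an odds ratio of 2.0.

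| Users | Assumed marijuana-only | No calendar | Evaluable | Power at p = .20 / .35 / .55 |
|---|---|---|---|---|
| 51.6 | 0% | 0 | 51.6 | .187 / .227 / .217 |
| 51.6 | 10% | 5.2 | 46.4 | .173 / .208 / .199 |
| 51.6 | 30% | 15.5 | 36.1 | .143 / .171 / .164 |
| 51.6 | 50% | 25.8 | 25.8 | .114 / .133 / .128 |
| 61.8 | 0% | 0 | 61.8 | .217 / .263 / .252 |
| 61.8 | 10% | 6.2 | 55.6 | .199 / .241 / .231 |
| 61.8 | 30% | 18.5 | 43.3 | .164 / .196 / .188 |
| 61.8 | 50% | 30.9 | 30.9 | .128 / .152 / .146 |

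Even with every user evaluable, power is about .19 to .26.

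**4. Youth who stop alcohol.** What happens depends on the unstated window.

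- *Lifetime use:* no former drinker is lost.
- *Past 12 months* (the S2BI window, assumed here): a youth who drank in the 6 months before baseline and then stopped is still caught at 6 months. Loss needs about a full year without drinking, so it arises mainly at the 12-month visit.
- *Since baseline:* a dual user who stops at once could be lost at both visits.

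The blank-calendar rule shows that the gate is not past-90-day drinking. SAP 2.2.5 says "Participants will complete the TLFB on the computerized tablet following completion of the assessment battery", which describes the tablet session. The follow-up batteries are abbreviated attachments that are not shown, so whether the gate recurs is unknown.

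**The case against.** **The primary outcome no longer uses the TLFB.** This largely stands for the trial's main result: the 6/27/2019 update names a Brief Frequency alcohol variable, and the 12/16/2020 update models alcohol use. It does not dispose of the point. SAP 6.2 already contains the mixed-effects approach of the 2020 update and still lists TLFB marijuana escalation among the primary outcomes. Its status is open.

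**Other marijuana data exist.** True. Initiation is not defined by the calendar, the S2BI covers marijuana over 12 months, and the battery table lists brief consumption-frequency items. The gap is confined to escalation. The SAP does not name these items as a substitute, and the table does not show that everyone was asked each one.

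**The numbers are small and assumed.** Also true. The prevalences come from a cohort aged 9-18, and the marijuana-only share is a guess.

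**Stronger readings that the documents do not support.** A reader might infer that anyone who stops drinking has no outcome. The blank-calendar rule, the missing window and the unseen follow-up batteries do not allow that.

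A reader might also infer that alcohol escalation is biased because quitters vanish. With assumed escalation of 40% versus 50% and assumed quitting of 30% versus 15%, dropping quitters gives .40/.70 = .571 and .50/.85 = .588. The odds ratio falls from 1.50 to 1.07. But those rates appear nowhere in the documents, and no section says quitters are dropped. A youth reporting no alcohol has zero drinks and, by definition, has not escalated.

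**Conclusion.** The point holds for marijuana escalation only. Followed as written, the plan leaves marijuana users who report no alcohol in the analysis group with no value and no fallback, and protocol section A contradicts the gate. The number affected is perhaps 5 to 15 of about 52-62 users among 300 completers, assuming that the earlier cohort's prevalence carries over and that 10-25% use marijuana alone. The documents do not fix that share.

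Missingness that depends on the intervention is a conditional risk: it requires the gate to be re-applied at follow-up with a past-12-month or since-baseline window. Bias in alcohol escalation is not shown.

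This merits correction and disclosure, but it does not threaten the alcohol outcome named in 2019. It would weigh more if marijuana escalation is confirmed as primary, and less if it is formally demoted.

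**What to change.** 1. In protocol section D and SAP 2.2.5, give the TLFB to every participant who reports alcohol or marijuana use, and to everyone who completed one at baseline, at baseline, 6 and 12 months. State the recall window at each visit and bring protocol section A into line.
2. State that a report of no use counts as zero for that substance: zero drinks or zero marijuana days.
3. For data already collected, use the brief frequency items for marijuana where they were asked, and label TLFB marijuana escalation as limited to alcohol reporters. Report by arm and visit how many marijuana users lack a calendar.
4. State in SAP 6.2 and 11.0 whether marijuana escalation remains primary after the 6/27/2019 update.

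The cost is one branching rule, a few sentences, and a few minutes of survey time for a small number of youth. A branching change cannot recover calendars never given, so steps 3 and 4 matter most for completed visits. None of this makes the comparison adequately powered; its estimates should be presented with that limitation.
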